**5.3 Primary endpoint**

1. Incidence of failure (see 5.5.1 for definition).

**5.4 Secondary endpoints**

1. Estimated adherence rate

2. Proportion of treatment discontinuations and changes due to different adverse events.

3. Decrease in HIV-1 RNA during the first 4 weeks of treatment (optional)

4. Proportion of patients with plasma HIV-1 RNA levels below 50 copies/ml after 4, 12, 24, 48, 72, 96, 120 and 144 weeks of treatment. Both Intention to Treat (ITT) and On Treatment (OT) analyses will be performed.

5. Changes in CD4+ T-cell count from baseline.

6. Time to discontinuation or changes of randomised treatment and reasons for this.

7. Incidence of adverse events.

8. Incidence of genotypic resistance to NRTIs, NNRTIs, and PIs that develops during the study

9. Proportion of patients with adjusted drug doses after therapeutic drug monitoring.

10. Correlations between plasma drug concentrations and virological outcome and adverse events.

11. Changes from baseline in plasma lipids.

12. Incidence of hypercholesterolemia and hypertriglyceridemia at baseline and follow-up.

13. Incidence of abnormal laboratory parameters (Hb, LPK, ASAT, ALAT, ALP, Bilirubin, S-amylas, Creatinin)

**5.5 Definitions for treatment and virological failure**

***5.5.1 Treatment failure***

Treatment failure is defined as:

1. Virological failure (see 5.5.2 for definition), or

2. Treatment interruption or change of study treatment due to side-effects (NRTI backbone are allowed to be changed, see 6.3), or

3. Treatment interruption or change of study treatment due to any other reason (NRTI backbone are allowed to be changed, see 6.3), or

4. Missed to follow-up

***5.5.2 Virological failure***

Virological failure is defined as:

1. HIV-1 RNA >50 copies/ml in two consecutive measurements from week 24 and on, or

2. any rise in HIV-1 RNA >50 copies/ml in two consecutive measurements after viral load <50 copies/ml has been reached, or

3. HIV-1 RNA never <50 copies/ml after week 24, or

4. <1 log copies/ml drop in HIV-1 RNA from baseline to week 4 (provided HIV-1 RNA >50 copies/ml), or

5. <2 log copies/ml drop in HIV-1 RNA from baseline to week 12 (provided HIV-1 RNA >50 copies/ml)

**6 Investigational plan**

**6.1 Trial design**

This is a phase IV, randomized open-label multicentre trial on antiretroviral effect of three different treatment regimens, one standard PI/r+2NRTI BID, and two QD regimens, NNRTI+2NRTI and PI/r+2NRTI respectively, on antiretroviral naïve HIV-1 infected patients.

Antiretroviral naïve HIV-1-infected patients with indications to start antiretroviral treatment could be included in the study. If the patient is subject to start treatment and thereby could be included in the study is judged by the clinician in agreement with the patient, and in agreement with the Swedish National Guidelines. An estimation of approximately 50-70 patients in each arm are to be included during two years.

Patients will initiate treatment with one of the three study arms (see 4 Treatment Regimens)

The randomisation is performed at the Department of Infectious Diseases, Sahlgrenska University Hospital/Östra and is stratified for CD4-cell count (< or ≥ 200 x 106/ml) and plasma HIV-1 RNA level (< or ≥ 100 000 copies/ml) (see 7.1.2).

Potentially eligible subjects will attend the clinic for a screening assessment. The CD4-cell count and HIV-1 RNA level at the screening visit will be used in stratification in the randomization process. Subjects will be randomized into one of three treatment arms and followed in accordance with the study plan.

Subjects will continue to receive the randomized treatment for the duration of the trial (i.e. 36 months). The NRTI backbone is allowed to be changed due to reasons other than virological failure, mainly side effects (see 6.3).

For patients in treatment arm 1 that acquire grade 3-4 hyperlipidemia, lopinavir/ritonavir could be switched to atazanavir/ritonavir in a roll-over-protocol (see 9 Roll-over protocol).

The patient could be followed in the study also if a visit has been missed of any reason, however, the baseline visit has to be performed.

The investigational site or the patient can anytime and of any reason decide to discontinue the study.

**6.2 Trial population**

***6.2.1 Inclusion criteria***

A subject will be eligible for inclusion in this trial only if all of the following criteria apply:

1. Male or female, aged 16 years of age.

2. HIV-1 infected as documented by a licensed HIV-1 antibody ELISA.

3. Ability to understand and provide informed consent to participate in the trial.

4. Indication for antiretroviral treatment.

5. Antiretroviral naïve.

6. All clinical laboratory values must be considered not clinically significant – for the potential response to the planned regimen – in the opinion of the investigator.

***6.2.2 Exclusion criteria***

Patients with any of the following criteria are excluded from participation in the study but recorded on a reject log.

1. Subjects being pregnant.

2. Women of childbearing potential not practicing birth control during the study.

3. Subjects with renal failure requiring dialysis.

4. Subjects with concurrent medications which – in the opinion of the investigator and according to drug product labelling – will result in drug interactions with any of the study drugs that are not manageable. Dose adjustments guided by therapeutic drug monitoring are allowed.

5. Resistance to any of the study drugs.

**6.3 Treatment during the study**

The aim is to continue with the randomised treatment throughout the entire study period, i.e. 36 months. Patients must not receive other antiretroviral drugs than those to which the patient has been randomised.

The NRTI backbone is allowed to be changed due to side effects or to other reasons (not virological failure). In that case, the second NRTI backbone should contain of 2 NRTIs, allowed to be dosed either as a QD or a BID regimen, irrespective of what arm the patient has been randomised to. Treatment with the PIs and NNRTI (lopinavir/ritonavir, atazanavir+ritonavir or efavirenz) continues, with the same dosage, as before the change of NRTIs.

Antiviral drugs used to treat other viral infections, such as HSV or CMV, may be used although they might have some additional anti-HIV-effect.

For patients in treatment arm 1 that acquire grade 3-4 hyperlipidemia, lopinavir/ritonavir could be switched to atazanavir/ritonavir in a roll-over-protocol (see 9 Roll-over protocol).

**7 Clinical and laboratory evaluations**

A flow chart showing the timing of trial procedures is shown in table 1 and 2.

Laboratory tests and clinical evaluations are performed as in clinical routine. The compulsory evaluations below are normally included in the clinical routine practice.

**7.1 Baseline characteristics and evaluations**

***7.1.1 Screening and baseline evaluation***

The site must obtain subject informed consent prior to the initiation of the study.

The pre-entry visit for screening must be conducted before, earliest 28 days prior to, the initiation of antiretroviral therapy.

The following evaluations should be performed at pre-entry (screening) visit:

 CD4-cell count

 Quantitative plasma viral load (HIV-1 RNA)

 Hepatitis serology (HBsAg and anti-HCV).

 Weight

CD4-cell count and quantitative HIV-1 RNA PCR obtained in clinical practice before initiation might be used for screening as long as it was obtained within the time limit (≤28 days before treatment initiation at baseline). Hepatitis serology results obtained earlier may be used instead.

The following evaluations should be performed at baseline (day 0):

 Entry criterias and demography including date of birth, gender, race, and mode of transmission of HIV

 CDC HIV classification 1993 version

 Previous HIV-associated conditions, i.e. B and C conditions according to the CDC HIV classification 1993.

 Weight (if not performed at screening)

 Blood lipids, i.e. total cholesterol, LDL, HDL, triglycerids (fasting)

 Hb, LPK, ASAT, ALAT, ALP, Bilirubin, S-amylas, Creatinin, fB-glukos

 Quantitative plasma viral load (HIV-1 RNA)

 2 x 10 ml plasma for storage in –70oC at study site.

***7.1.2 Randomisation***

Patients eligible to the study and who have signed informed consent may be randomised as soon as results from viral load and CD4 cell count measurements are available.

The randomisation (1:1:1) is performed at the Department of Infectious Diseases, Sahlgrenska University Hospital/Östra and is stratified for CD4-cell count (< or ≥ 200 x 106/ml) and plasma HIV-1 RNA level (< or ≥ 100 000 copies/ml).

**7.2 On trial evaluations**

On trial evaluations will be completed at week 4 (3-5), 12 (10-14), 24 (22-26), 48 (45-51), 72 (69-75), 96 (93-99), 120 (117-123) and 144 (141-147). In brackets are indicated acceptable deviations from time of follow-up.

In-between visits according to local praxis, and laboratory tests other than those settled in the study protocol, will be conducted outside the study.

The following evaluations will be performed at each visit if nothing else is stated:

 Current antiretroviral therapy including eventual dose modifications, interruptions, or discontinuations.

 Adherence to treatment

 New HIV-associated complications.

 Side-effects and laboratory pathology

 Weight (week 4, 48, 96, and 144)

 CD4-cell count

 Quantitative plasma viral load (HIV-1 RNA)

 Blood lipids, i.e. total cholesterol, LDL, HDL, triglycerids (fasting)

 Hb, LPK, ASAT, ALAT, ALP, Bilirubin, S-amylas, Creatinin, fB-glukos

 Plasma concentration of NNRTI and PI 12-24 hours after last drug intake (at week 4, 48, 96 and 144)

 2 x 10 ml plasma for storage in –70oC at study site

On trial evaluations will optionally also be performed at day 7 (6-8), 14 (12-16) and 21 (19-23) including:

 Current antiretroviral therapy including eventual dose modifications, interruptions, or discontinuations

 Adherence to treatment

 New HIV-associated complications.

 Side-effects and laboratory pathology

 Quantitative plasma viral load (HIV-1 RNA)

 Hb, LPK, ASAT, ALAT, ALP, Bilirubin, S-amylas, Creatinin, fB-glukos (at day 14)

 2 x 10 ml plasma for storage in –70oC at study site

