**4 Treatment regimens**

**4.1 Randomised treatment arms**

Patients will be randomized to one of three study arms (1:1:1). Randomization will be stratified according to CD4-cell count (above or below 200 x 106/l) and plasma HIV-RNA level (above or below 100 000 copies/ml).

Study arms:

1. lopinavir/ritonavir (Kaletra®) 400/100 mg BID + 2 NRTIs BID

2. atazanavir (Reyataz ®) 300 mg QD + ritonavir (Norvir®) 100 mg QD + 2 NRTIs QD

3. efavirenz (Stocrin®) 600 mg QD + 2 NRTIs QD

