**Table 2**

Clinical and laboratory evaluations at follow-up

| **Evaluation** | **Follow-up** |  |  |  |  |  |  |  |  |  |  |
| --- | --- | --- | --- | --- | --- | --- | --- | --- | --- | --- | --- |
|  | **d. 7**  **(6-8)**  **optional** | **d. 14**  **(12-16)**  **optional** | **d. 21**  **(19-23)**  **optional** | **w. 4**  **(3-5)** | **w.12**  **(10-14)** | **w.24**  **(22-26)** | **w.48**  **(45-51)** | **w.72**  **(69-75)** | **w.96**  **(93-99)** | **w.120**  **(117-123)** | **w.144**  **(141-147)** |
| CDC Classification |  |  |  | X | X | X | X | X | X | X | X |
| Medicationsa |  | X |  | X | X | X | X | X | X | X | X |
| Adherence estimation |  | X |  | X | X | X | X | X | X | X | X |
| Adverse events |  | X |  | X | X | X | X | X | X | X | X |
| HIV-associated conditionsb |  | X |  | X | X | X | X | X | X | X | X |
| Plasma HIV-1 RNA quantitative PCRc | X | X | X | X | X | X | X | X | X | X | X |
| CD4 cell count |  |  |  | X | X | X | X | X | X | X | X |
| Blood lipids (Total Cholesterol, LDL, HDL, TG) (fasting) |  |  |  | X | X | X | X | X | X | X | X |
| Hb, LPK, ASAT, ALAT, ALP, Bilirubin, S-amylas, Creatinin, fB-glukos |  | X |  | X | X | X | X | X | X | X | X |
| Plasma concentration of NNRTI and PId |  |  |  | X | (X)f |  | X |  | X |  | X |
| Plasma sample collectione | X | X | X | X | X | X | X | X | X | X | X |
| Weight |  |  |  | X |  |  | X |  | X |  | X |
|  |  |  |  |  |  |  |  |  |  |  |  |

a Antiretroviral therapy including dose modifications, interruptions, discontinuations, and reasons for change should be indicated. All other drugs that are taken regularly should be indicated.

b At baseline, also the history of previous HIV-associated conditions.

c The HIV-1 RNA determination is done real-time at the site using routine virological methodology at that site, preferably the Roche Amplicor Ultrasensitive assay. The same method should be used for the individual subject throughout the trial.

d 10-24 hours after the last dose, 10 ml heparin tube, centrifuged, plasma sent to Clin. Pharm., KU Huddinge

e 2 x 10 ml or 3 x 6 ml EDTA tubes, plasma collected and stored in –70oC at study site.

f if not performed on the previous visit

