**Table 3**

Roll-over protocol

| **Evaluation** | **Extra visitsa** |  |
| --- | --- | --- |
|  | **d0**  **(-7-0)** | **w4**  **(3-5)** |
| Blood lipids (Total Cholesterol, LDL, HDL, TG) | X | X |
| Hb, LPK, ASAT, ALAT, ALP, Bilirubin, S-amylas, Creatinin, fB-glukos |  | X |
| Plasma concentration of atazanavirb |  | X |
| Plasma sample collectionc | X | X |
|  |  |  |
|  |  |  |

a The day when lopinavir/r is changed to atazanavir+r is regarded as d0 in the roll-over protocol. Besides the extra visits, the patient continues in the follow-up schedule as planned in table 2.

b 10-24 hours after the last dose, 10 ml heparin tube, centrifuged, plasma sent to Clin. Pharm., KU Huddinge

c 2 x 10 ml or 3 x 6 ml EDTA tubes, plasma collected and stored in –70oC at study site.

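### Section 7.2 and Table 2 give different windows for the same drug-level samples, and the one window shared by BID and QD arms lets lopinavir samples fall past the dosing interval

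*Protocol*

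**What the plan says.** Protocol section 7.2 lists among the on-trial evaluations "Plasma concentration of NNRTI and PI 12-24 hours after last drug intake (at week 4, 48, 96 and 144"). Table 2 marks the PI/NNRTI concentration at the same four weeks, with week 12 as a fallback if the week 4 sample was not taken, and its footnote d reads "10-24 hours after the last dose, 10 ml heparin tube, centrifuged, plasma sent to Clin. Pharm., KU Huddinge". Table 3, footnote b, which covers atazanavir after roll-over, also has "10-24 hours after the last dose, 10 ml heparin tube".

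None of these places separates the arms. Section 4.1 gives arm 1 as "lopinavir/ritonavir (Kaletra®) 400/100 mg BID + 2 NRTIs BID", arm 2 as "atazanavir (Reyataz ®) 300 mg QD + ritonavir (Norvir®) 100 mg QD + 2 NRTIs QD" and arm 3 as "efavirenz (Stocrin®) 600 mg QD + 2 NRTIs QD".

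The levels serve two secondary purposes. Objective 8 in section 5.2 is to determine PI and NNRTI concentrations at steady state. Endpoint 10 in section 5.4 is "Correlations between plasma drug concentrations and virological outcome and adverse events".

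**The concern.** There are two linked problems.

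- **Contradiction.** A sample taken 11 h after the last dose is valid under Table 2 and out of window under section 7.2. Sites following different pages would collect different data.
- **One window for two dosing frequencies.** For a QD drug, either window lies inside the dosing interval. For a BID drug, most of either window lies beyond it, at times when the next dose should already have been taken.

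In arm 1, a late sample that is still in window therefore comes from a patient whose next dose is late or missed. Section 3.1 itself names adherence as a major determinant of virological efficacy. A low lopinavir level could then mark poor adherence or a late sampling time, not low exposure under regular dosing. An association with virological failure in endpoint 10 could arise that way. For objective 8, a level measured after a late or missed dose does not describe steady state on the assigned regimen.

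**Working it through.** **Inputs.** The windows are 12-24 h (section 7.2) and 10-24 h (Table 2, footnote d). Dosing is BID in arm 1 and QD in arms 2 and 3 (section 4.1). The protocol does not give intervals in hours; 12 h for BID and 24 h for QD are the nominal values. It gives no figure of its own on this point to reproduce.

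**Step 1: overlap of window and dosing interval.** For a window from a to b hours and an interval of T hours, the overlap is max(0, min(b, T) − a), out of a width of b − a.

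| Window | BID, T = 12 h | QD, T = 24 h |
| --- | --- | --- |
| 12-24 h (7.2) | min(24, 12) − 12 = 0 of 12 h | 24 − 12 = 12 of 12 h |
| 10-24 h (Table 2) | min(24, 12) − 10 = 2 of 14 h | 24 − 10 = 14 of 14 h |

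Under 7.2, a lopinavir sample from a patient dosing on schedule can be taken only at the 12 h end point, the nominal trough. Under Table 2 it can be taken from 10 to 12 h. The remaining 12 hours of either window lie past the interval.

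**Step 2: what timing alone could do to the level.** The protocol states no half-life, so this is an illustration under an assumption of 4-8 h. With first-order decline and no further dose, the level at t hours relative to that at 12 h is 2^(−(t − 12)/h), where h is the half-life.

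| Assumed half-life | 18 h sample vs 12 h | 24 h sample vs 12 h |
| --- | --- | --- |
| 4 h | 2^(−6/4) = 0.35 | 2^(−12/4) = 0.125 |
| 6 h | 2^(−6/6) = 0.50 | 2^(−12/6) = 0.25 |
| 8 h | 2^(−6/8) = 0.59 | 2^(−12/8) = 0.35 |

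The smallest difference is 1/0.59 ≈ 1.7-fold (18 h sample, 8 h half-life). The largest is 1/0.125 = 8-fold (24 h sample, 4 h half-life).

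**Step 3: sensitivity to the assumption.** With a longer assumed half-life of 24-48 h, a 24 h sample is 2^(−12/24) = 0.71 to 2^(−12/48) = 0.84 of the 12 h level. The size therefore depends strongly on the half-life. The contradiction and the overlap result in step 1 do not depend on it.

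**The case against.** The strongest reply is that a shared outer window permits late lopinavir samples but does not require them. This stands in part. A sample at exactly 12 h, before the next dose, is a valid trough even under 7.2, and Table 2 admits 10-12 h, so a patient dosing on schedule can be sampled properly. Counting hours of window does not count samples, and nothing shows how many would be late. The 24 h figure is the extreme case: that patient has missed a whole dose.

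Stronger readings are tempting, and the protocol does not support them:

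- A reader might infer that lopinavir levels cannot be compared with those of the other arms. No comparison of concentrations between arms is named, and levels of three different drugs are not interchangeable under any window. The problem lies within arm 1.
- A reader might infer that patients would hold a dose to meet the window. Nothing tells sites or patients to do so.
- A reader might infer that endpoint 10 will be biased by the fold-differences above. Whether and how far it is biased depends on actual sampling times and on whether they are used in the analysis, so no bias has been quantified.

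It is also fair to say that the CRF is not shown, so it may already capture the time of last intake, and that the exact model for endpoint 10 belongs in the SAP. Neither point removes the contradiction or the lack of any link between the window and the dosing interval.

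Finally, 12-24 h appears struck through in footnote d of Table 1. That might suggest that 7.2 was overlooked in a revision, but the NNRTI/PI measurement itself is struck from that table too, so it does not settle which window was intended.

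**Conclusion.** The point holds within limits. The two windows contradict each other in current text for the same samples. With nominal intervals of 12 h and 24 h, 0 of 12 h (7.2) or 2 of 14 h (Table 2) lie inside the lopinavir interval, against all of either window in the QD arms. The criticism of the BID arm applies in full to 7.2, apart from the 12 h end point, and to 12 of the 14 hours in Table 2.

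The consequence is that lopinavir samples within arm 1 are not comparable with one another unless time since intake is known and used, because late samples carry both timing and adherence. The possible size, about 1.7- to 8-fold for samples at 18-24 h, rests wholly on the assumed half-life of 4-8 h and on first-order decline. Objective 8 and endpoint 10, both secondary, are weakened. Treatment failure, the primary endpoint, does not use drug levels. This is more than clerical, and it should be corrected because the correction is cheap.

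**What to change.** 1. Reconcile section 7.2 with Tables 2 and 3 so that a single statement governs these samples.
2. State the sampling window in relation to each arm's own dosing interval. The hours are for the sponsor to decide; this review does not say which existing window is right.
3. Record the actual time since last intake with each sample, if the CRF does not already do so.
4. Take that time into account within each drug in the endpoint 10 correlations, with the form of the model left to the SAP.

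The cost is protocol wording and at most one data field. The samples are unchanged.

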The Swedish guidelines recommend initiation of treatment when the CD4-cell count is in the range between 200 and 350 x 106/l in asymptomatic HIV-infection, and in patients with symptomatic HIV-infection irrespective of the CD4-cell count. As first line therapy, 2 NRTIs in combination with either a NNRTI or a PI is suggested. When PIs are chosen, ritonavir-boosted combinations are most often prefered (PI/r) due to pharmacokinetic and virological reasons[4]. During the last year several drugs have been licensed for dosing once daily (QD), however, only one clinical controlled study between QD and twice-daily (BID) regimens has as yet been published[5]. There are so far no comparable studies between NNRTI-based and PI/r-based regimens given to patients that are antiretroviral naïve published.

The present study aims to compare efficacy, side-effects, and treatment adherence of three different treatment regimens given to antiretroviral naïve HIV-1 infected patients. Treatment will be initiated in accordance with the Swedish National Guidelines. In the BID arm (1), which could be considered as a standard regimen at present, lopinavir/ritonavir, is co-administrated with 2 NRTIs administrated BID. The first QD arm (2) combines the PI atazanavir/ritonavir with 2 NRTIs administrated QD, and in the second QD arm (3), the NNRTI efavirenz is combined with 2 NRTIs administrated QD. All drugs used in the study are licensed in the participating countries and patients will be followed as in clinical practice. Patients could optionally, after informed consent, be followed with additional measurements of HIV-1 RNA after 1, 2, and 3 weeks of treatment to asses the kinetics of viral decline after initiation of treatment.

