**9 Data analysis and statistical methods**

The trial will randomise (1:1:1) 150-210 subjects in three treatment arms.

The subjects will be followed for 144 weeks. Interim analysis will be assessed when all subjects have completed 24, 48 and 96 weeks of therapy.

Both intention to treat analyses and on-treatment analyses will be performed.

The comparisons between treatment arms with respect to treatment failure will be performed by survival tests, which take the follow up periods into account. Other comparisons will be performed by chi-square test (presence of side effects) including all three treatment groups and Kruskal-Wallis test for continuous variables. The last mentioned test is a generalization of Mann-Whitney’s test applicable on three groups. Two-tailed test at the significance level 0.05 will be used.

Figure 1

N=65 in each one of two groups compared. The probability of treatment success is P1 and P2 in the two groups. From the figure we can read that if P1 is 0.70, e.g., then P2 has to exceed 0.90 for achieving the power 80%. The line y = x is given in order to facilitate the reading of the figure. The power calculation was performed for Fisher’s exact test at the level 0.05, two-tailed test, though survival tests will be used. However, the power determination for the survival test needs more specifications than available at present and the difference in power is small.

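### Section 7.2 and Table 2 disagree on what is recorded at the optional early visits; opted-in patients are observed more closely before week 4, and opting in is not placed before open-label allocation

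*Protocol*

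**What the plan says.** The optional visits are introduced in section 3.1 as a viral-kinetics exercise: "Patients could optionally, after informed consent, be followed with additional measurements of HIV-1 RNA after 1, 2, and 3 weeks".

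Section 7.2 gives them a wider content. It opens with "On trial evaluations will optionally also be performed at day 7 (6-8), 14 (12-16) and 21 (19-23) including" and then lists current therapy, adherence, new HIV complications, side-effects and laboratory pathology, HIV-1 RNA, routine laboratory tests and stored plasma. Only one item in that list is tied to a single day: "Hb, LPK, ASAT, ALAT, ALP, Bilirubin, S-amylas, Creatinin, fB-glukos (at day 14)". The others carry no restriction and so apply to days 7, 14 and 21.

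Table 2 differs. In its first four columns (day 7, day 14, day 21, week 4), the adverse-event row reads "Adverse events | | X | | X", adherence reads "Adherence estimation | | X | | X" and medications reads "Medicationsa | | X | | X". HIV-associated conditions follow the same pattern. Days 7 and 21 carry only HIV-1 RNA and stored plasma.

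Week 4 is the first compulsory on-trial visit and records therapy, adherence and side-effects in every patient. Section 8 requires any adverse event during the trial to be documented, with onset and resolution dates. For the analysis, section 9 says: "Other comparisons will be performed by chi-square test (presence of side effects) including all three treatment groups".

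**The concern.** There are two linked problems.

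The first is a plain contradiction in the data-collection schedule. A site working from 7.2 and a site working from Table 2 will record different things at days 7 and 21. An analysis plan cannot repair that afterwards.

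The second is that safety information is gathered at visits that only some patients attend. The trial is open label (2.1). Section 7.1.2 allows randomisation once consent is signed and the viral load and CD4 results are available, and Table 1 note i allows it before day 0. Section 3.1 says opting in follows informed consent, but not that it precedes allocation. If willingness to attend extra visits differed by known arm, one arm would be questioned and tested more often in the first four weeks. Incidence of adverse events (5.4, item 7) and of abnormal laboratory parameters (5.4, item 13) are the secondary endpoints most exposed.

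**Working it through.** **Step 1. The two schedules side by side, day 0 to week 4.**

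| Item | 7.2, optional visits | Table 2, optional visits | Week 4, all patients |
| --- | --- | --- | --- |
| Therapy, adherence, side-effects, HIV complications | days 7, 14, 21 | day 14 | yes |
| Routine laboratory panel | day 14 | day 14 | yes |
| HIV-1 RNA, stored plasma | days 7, 14, 21 | days 7, 14, 21 | yes |

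The documents agree on the last two rows and conflict on the first.

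**Step 2. Scheduled contacts up to and including week 4.**

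- Side-effect enquiries: 1 without opting in; 1 + 1 = 2 if opted in under Table 2; 3 + 1 = 4 if opted in under 7.2.
- Post-baseline laboratory panels: 1 without opting in; 1 + 1 = 2 if opted in, under both schedules.

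These are study minimums. Section 7.2 permits in-between visits by local practice but places them, and any other laboratory tests, outside the study.

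**Step 3. Size of a possible spurious difference.** The protocol gives no opt-in rates and no figure for this point, so there is nothing of its own to reproduce. The following inputs are assumptions:

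- *r*, true share of patients with an early transient side effect, equal in all arms: 0.4 to 0.6
- *d1*, share of these recorded with week 4 only: 0.5 to 0.7
- *d2*, share recorded with optional visits: 0.9
- *q*, opt-in share in an arm

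Recorded incidence = r × [d1 + (d2 − d1) × q], so the difference between two arms = r × (d2 − d1) × (difference in q).

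- Opt-in 20% v 60%: from 0.4 × 0.2 × 0.4 = 3.2 points to 0.6 × 0.4 × 0.4 = 9.6 points
- Opt-in 30% v 50%: from 0.4 × 0.2 × 0.2 = 1.6 points to 0.6 × 0.4 × 0.2 = 4.8 points
- Equal opt-in: 0
- d1 = d2 (week 4 captures as much): 0

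**Step 4. Effect on a three-arm chi-square test.** Section 9 supplies the 0.05 level, and the 65 per group comes from its power statement. Assumed: equal true rate *p* of 0.3 to 0.5 in all arms, full capture in opted-in patients, and capture *s* of 0.6 to 1.0 in the others. Recorded rate = p × [q + (1 − q) × s]. The false-positive rate comes from the noncentral chi-square with 2 degrees of freedom.

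| Opt-in by arm | False-positive rate over the range of p and s |
| --- | --- |
| equal | 5.0% |
| 40/40/60% | 5.0 to 7.3% |
| 30/30/70% | 5.0 to 14.8% |

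The worst case is p = 0.5 and s = 0.6. The recorded rates are 0.5 × (0.3 + 0.7 × 0.6) = 0.36 in two arms and 0.5 × (0.7 + 0.3 × 0.6) = 0.44 in the third. With s = 1 the rate stays at 5.0% for every opt-in split.

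**The case against.** A reader might infer that whether early side effects are collected at all depends on opting in. The documents do not support that. Week 4 is compulsory, and section 8 covers any event during the trial with its onset and resolution dates, so events already resolved are in scope. Opting in changes the number of enquiries and the recall interval. This part of the objection stands.

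A reader might also infer that the arm comparison is biased as planned. That is not supported either. The documents show no imbalance in opt-in, and the consent form, which might settle when the choice is made, is not in the text at hand. Nor does section 9 say that its test uses everything recorded; which visits enter the adverse-event table may properly be left to an analysis plan.

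The sizes in step 3 may also be too large for the endpoint tested. If presence of side effects means any side effect over 144 weeks, a missed early event matters only in patients with nothing else recorded. If 50 to 80% have another recorded event (an assumption), the figures are multiplied by 0.2 to 0.5: 3.2 to 9.6 becomes about 0.6 to 4.8 points, and 1.6 to 4.8 becomes about 0.3 to 2.4. The standard error of a difference near 50% with 65 per arm is √(2 × 0.25 / 65) = 8.8 points. Tests of single event types would be diluted less.

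Two things survive. The contradiction between 7.2 and Table 2 does not depend on any of this. And for laboratory values neither recall nor section 8 closes the gap: an abnormality present at day 14 and gone by week 4 is measured under the study schedule only in opted-in patients.

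**Conclusion.** The contradiction is certain and must be reconciled so that all sites record the same items.

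Unequal intensity of ascertainment is also certain: at least one extra side-effect enquiry and one extra laboratory panel before week 4 for opted-in patients, under either schedule. Bias between arms is only a conditional risk. It needs unequal opt-in together with incomplete capture at week 4, and it vanishes if either is absent. On the stated assumptions it is 1.6 to 9.6 points in recorded early side effects, less for an any-event endpoint, with a false-positive rate near nominal for moderate imbalance (at most 7.3% at 40/40/60%) and 14.8% in the worst case examined.

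The point concerns secondary safety comparisons. No effect on the primary endpoint is shown, and no size has been derived for adherence or treatment changes, for which the finding is the inconsistent schedule.

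**What to change.** 1. Make 7.2 and Table 2 agree on what is recorded at days 7, 14 and 21. The same edit can settle the day 7 window, which is 6-9 in section 2.6 and 6-8 in 7.2 and Table 2.
2. Have the decision on the optional visits recorded at consent, before randomisation. Opt-in is then balanced between arms in expectation, although attendance may still differ afterwards.
3. In section 9 or the analysis plan, add a sensitivity analysis of the arm comparisons of adverse events and laboratory abnormalities that uses only visits scheduled for all patients (week 4 onwards). Keep all recorded adverse events in the main safety report. The restriction equalises laboratory testing fully but adverse events only partly, because an event noted at day 14 is more likely to be known at week 4. That is why it should not replace the main analysis.
4. Do not stratify by opt-in unless it is fixed before randomisation; otherwise the analysis conditions on a choice made after allocation.

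The cost is a corrected list or table, one tick-box on the consent or randomisation form, one sentence and one extra table. No data are lost.
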